## Methods

### Sample and Sampling

In this evaluation study, 4th graders were assessed on the classroom level. Since 19.4% of students in Lower Saxony participate in the Klasse2000 program, it seemed feasible to base group comparisons on a sufficiently high number of students [11]. For this evaluation, a random representative sample of 600 classes was drawn out of a total of about 4000. Based on the current implementation rate of the Klasse2000 program, it was expected that around 120 of the 600 randomly selected schools were participating in the program. To ensure a sufficient rate of participating Klasse2000 classrooms, 140 additional classrooms known to have participated in the program were randomly selected and added to the sample (oversampling). In addition to surveying the 4th grade students of participating and nonparticipating classes, parents, teachers, and school principals were assessed. Overall, we aimed for the total sample to consist of 8000 students and their parents.

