#### Data Handling and Monitoring

Data assessment and management is completed by the KFN data protection official. The data protection official is employed directly by the KFN and has neither monetary nor scientific involvement in the project. All project staff members were obliged to uphold data protection rules and regulations. Participants do not reveal their names at any point in the study. The students provide their month of birth, age, and gender. The parents provide the same information, which will be used for matching should matching via the matching code not be possible. Children and their parents can be matched to a school by a field code. This field code is necessary to determine whether a school participates in the Klasse2000 program without endangering the blinding of the test administrators. After successful matching of parents, children, principals, and schools, all corresponding field codes are deleted. The data are then fully anonymous (ie, the school name can no longer be inferred from the cases).

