### Data Analysis

The decision to participate in the Klasse2000 program is made at the school level. Hence, schools self-select for implementing the intervention. This selection bias must be controlled for when comparing the outcomes of children participating in the Klasse2000 and those who did not. The gold standard for preventing selection bias is randomization. There are three major factors that made a randomized trial highly infeasible for this evaluation: (1) as a general intervention, the Klasse2000 targets a high number of outcomes, (2) effect sizes in universal prevention programs can be expected to be rather small, (3) the intervention is implemented during the entire primary school time (ie, over a time span of 4 years). Hence, a very high number of schools would need to be randomized to participate in an intervention over several years. An attractive alternative to an randomized controlled trial is a natural experiment. However, the Klasse2000 is implemented all over Germany, and there are no immediately comparable intervention programs. Hence, neither regional implementation nor the comparison of a comparable program lend themselves for overcoming selection bias. Given these circumstances, a propensity score-matching approach will be implemented as a feasible alternative. The basic idea of a matching approach is as follows: for each student who is currently participating in the Klasse2000 program, a control student will be selected who matches the treatment group participant as closely as possible regarding criteria that are relevant yet unrelated to the participation in the prevention program (ie, gender, socioeconomic status). The matching will be performed with a matching algorithm that assigns weights to each individual in the control group (ie, inverse probability weighting). The estimation of treatment effects will be completed using regression-based analyses that take these weights into account. Simulation studies show that the propensity score-matching approach enables an unbiased estimation of intervention effects [18].

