Prior to analysis, data will be checked for outliers, inconsistencies, and possible transformation. We predict that our sample size will be large enough for our statistical tests to be robust regarding nonnormally distributed variables. Power analyses (ie, a priori) based on a type I error rate (false positive) of α=.05, statistical power of 1−β=.80, and a minimum detectable effect size of ES=0.2 resulted in a required sample size of n=310 (1-tailed) students in each group (intervention and control).

Missing data will be handled using state-of-the-art imputation techniques (multiple imputation in missing non-at-random scenarios [ie, by parametric recursive partitioning] [19,20]). Wherever earlier findings suggest differential effects (ie, regarding gender), subgroup analyses of the above-mentioned hypotheses will be performed. Furthermore, post hoc analyses of different implementation factors potentially contributing to positive treatment effects over time will be conducted.

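### Schools choose the program and whole classes are surveyed, but neither the described effect analysis nor the sample size provides for clustering, and it is unclear whether anonymous cluster numbers survive the deletion of the field codes

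*Protocol article*

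**What the plan says.** All references are to the Methods of the protocol article.

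- **Level of exposure** (Data Analysis): "The decision to participate in the Klasse2000 program is made at the school level".
- **Unit of sampling and survey** (Sample and Sampling): "In this evaluation study, 4th graders were assessed on the classroom level". A random sample of 600 classes was drawn, and 140 classes known to be in the program were added.
- **Effect analysis** (Data Analysis): a matching algorithm gives weights to control pupils, and then "The estimation of treatment effects will be completed using regression-based analyses that take these weights into account". The abstract likewise says only that estimation in the matched sample allows for the matching process.
- **Sample size** (Data Analysis): the inputs are a 5% false positive rate, 80% power and a standardized effect of 0.2. The calculation "resulted in a required sample size of n=310 (1-tailed) students in each group (intervention and control".
- **Link to the school** (Data Handling and Monitoring): a field code ties children and parents to a school. "After successful matching of parents, children, principals, and schools, all corresponding field codes are deleted". The stated result is that the school name can no longer be inferred.

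The article mentions no multilevel model, cluster-robust variance, ICC or design effect. It does not say whether a neutral school or class number stays in the analysis file.

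**The concern.** Exposure is set by the school and shared by all pupils of a class, so the program effect is a contrast between clusters. When classmates resemble each other, each further pupil from the same class adds less information than an independent pupil would. A pupil-level variance ignores this and comes out too small.

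The article treats school self-selection as a source of bias and answers it with weights. Weights can correct measured imbalance. They do not correct a variance that assumes independence.

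The problem is most plausible for hypotheses 3.1 to 3.3 (school and classroom atmosphere, bullying and victimization), because these describe an environment that classmates share. They belong to the 11 primary hypotheses (four, four and three under research questions 1 to 3). The article expects rather small effects and would value them from a public health perspective, so conclusions may turn on whether the standard errors are right.

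The data rule makes the timing matter. A variance estimator can be added later, but a grouping variable removed from fully anonymous data cannot be restored.

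**Working it through.** **Step 1: reproduce the plan's figure.** Inputs from Data Analysis: one-sided α = 0.05, power 0.80, standardized effect 0.2, equal groups.

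- Normal approximation: n = 2 × (1.645 + 0.842)² / 0.2² = 309.1 per group, which rounds up to 310.
- One-sided t test for independent groups: 309.8, which also rounds up to 310.
- The two-sided version gives 393 and does not match.

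The stated 310 is therefore the figure for independent pupils, that is, a design effect of 1.

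**Step 2: inputs for the design effect.**

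- Pupils per class, m: not stated. The lower value, 10.8, is the target sample over the sampled classes: 8000 / (600 + 140). The upper value, 17, is an assumption. It lies below the average enrolled class size that follows from the description of the program: 60,000 / 2800 = 21.4. The number of classes that took part is not in the text available here.
- ICC: not stated. Assumed range 0.02 to 0.10.

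**Step 3: formulas.**

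- Design effect: DE = 1 + (m − 1) × ICC
- True size of a nominal one-sided 5% test that ignores clustering: 1 − Φ(1.645 / √DE)
- Coverage of a nominal 95% interval that ignores clustering: 2Φ(1.96 / √DE) − 1
- Required pupils per group: 310 × DE, rounded up

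**Step 4: results.**

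| m | ICC | DE | True one-sided error | Coverage of 95% interval | n per group |
|---|---|---|---|---|---|
| 10.8 | 0.02 | 1.20 | 6.6% | 93% | 371 |
| 10.8 | 0.10 | 1.98 | 12.1% | 84% | 614 |
| 17 | 0.02 | 1.32 | 7.6% | 91% | 410 |
| 17 | 0.10 | 2.60 | 15.4% | 78% | 806 |

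For the first row, DE = 1 + 9.8 × 0.02 = 1.196 and 310 × 1.196 = 370.8. For the last row, DE = 1 + 16 × 0.10 = 2.60 and 310 × 2.60 = 806.

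**Step 5: is power in danger?** The article reports 2371 program pupils and 4005 controls. At DE = 2.60 these are worth 2371 / 2.60 = 912 and 4005 / 2.60 = 1540 independent pupils. Both exceed 310. Power for an effect of 0.2 stays above 0.99, including under 1:1 matching of 2371 pairs. This leaves aside precision lost through unequal weights.

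**The case against.** The strongest reply is that the sentence on the effect analysis says what the regression includes and does not say what it excludes. A weighted regression with cluster-robust errors, or a weighted multilevel model, would fit it. The article is a condensed text, and the choice of variance estimator is often left to an analysis plan, which is not shown here. This stands as a limit: a reader might infer that cluster adjustment has been rejected, and the article does not support that. It does not remove the point. The design is described as clustered, the one feature the analysis is said to account for is the weights, and the stated 310 is an independent-pupil figure that no later plan can make right for this design.

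A reader might also infer that deleting the field codes makes cluster-correct standard errors impossible. The data rule does not say so. Its stated aim is to remove the identity of the school, and a random number without a key would be compatible with that aim. The deletion is a risk that the article leaves open. Trial Status Upon Submission of Protocol Revision reports that data integration, including the linking of child and parent data, was complete. Deletion is due after successful matching, so the codes may or may not still exist.

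Finally, the size rests on assumed values. The upper figures need both the larger class and the larger ICC, covariates may lower the residual ICC, and the inflation is slight when the ICC is near zero. To claim that every hypothesis is materially affected would go beyond what the article shows. The conditional statement stands.

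**Conclusion.** The point holds in conditional form. The design is clustered by the article's own account, the described analysis makes no provision for clustering, and the sample size assumes independent pupils. If the analysis is run as described and the ICC is above zero, p values and intervals are too optimistic. With 10.8 to 17 pupils per class and an ICC of 0.02 to 0.10, both assumed, the standard error is too small by a factor of √1.20 = 1.09 to √2.60 = 1.61, which leads to the error rates and coverage tabulated above. The harm is to type I error and interval width. Power to detect an effect of 0.2 is not threatened at the achieved sample size, before losses from weighting.

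**What to change.** 1. **Analysis.** State that effects are estimated by weighted regression with cluster-robust standard errors at school level, or by a weighted multilevel model with class within school. Any bootstrap should resample schools.
2. **Data.** Confirm that random, keyless school and class numbers are kept in the analysis file. If the field codes still exist, assign these numbers before deleting them. This is compatible with the stated aim that the school can no longer be identified.
3. **Sample size.** Restate the requirement with a design effect and give the assumed ICC and class size. Under the assumptions above it is about 371 to 806 pupils per group, which the achieved 2371 and 4005 exceed before losses from weighting.

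The article reports that no hypothesis-related results had been obtained at resubmission, so at that stage the change could still be prespecified. The cost is a change of wording and, if the codes still exist, one recoding step. If they have been deleted without a substitute, the cost is larger and cannot be judged from the article. The statistical price is wider confidence intervals.

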Research question 1 (well-being; primary outcome domain): How does participation in the Klasse2000 prevention program influence children’s well-being?Hypothesis 1.1: The prevention program Klasse2000 has a positive influence on the children’s well-being.Hypothesis 1.2: The prevention program Klasse2000 has a positive influence on the children’s self-esteem.Hypothesis 1.3: The prevention program Klasse2000 has a positive influence on the children’s emotion regulation.Hypothesis 1.4: The prevention program Klasse2000 reduces the severity of behavioral problems.Research question 2 (health-related behavior; primary outcome domain): How does participation in the Klasse2000 prevention program influence children’s health-related behavior?Hypothesis 2.1: The prevention program Klasse2000 increases fruit and vegetable consumption.Hypothesis 2.2: The prevention program Klasse2000 increases the consumption of water and unsweetened tea.Hypothesis 2.3: The prevention program Klasse2000 decreases the consumption of sweets, salty snacks (eg, chips, pretzels), and sweetened beverages.Hypothesis 2.4: The prevention program Klasse2000 increases the time children spend exercising.Research question 3 (school and classroom atmosphere, school-based conflicts, and violence; primary outcome): How does participation in the Klasse2000 prevention program influence the school and classroom atmosphere and school-based violence?Hypothesis 3.1: The prevention program Klasse2000 has a positive influence on the school and classroom atmosphere.Hypothesis 3.2: The prevention program Klasse2000 decreases the probability of engaging in bullying.Hypothesis 3.3: The prevention program Klasse2000 decreases the probability of becoming a victim of bullying.Research question 4 (media use; secondary outcome): How does participation in the Klasse2000 prevention program influence media use?Hypothesis 4.1: The prevention program Klasse2000 decreases the time spent on media.Hypothesis 4.2: The prevention program Klasse2000 decreases the probability of watching movies with an age rating of 16 or 18.Hypothesis 4.3: The prevention program Klasse2000 decreases the frequency of watching movies with an age rating of 16 or 18.Hypothesis 4.4: The prevention program Klasse2000 decreases the probability of playing video games with an age rating of 16 or 18.Hypothesis 4.5: The prevention program Klasse2000 decreases the frequency of playing video games with an age rating of 16 or 18.Research question 5 (alcohol and tobacco consumption; secondary outcome): How does participation in the Klasse2000 prevention program influence the children’s alcohol and tobacco consumption?Hypothesis 5.1: The prevention program Klasse2000 decreases the probability of drinking alcohol.Hypothesis 5.2: The prevention program Klasse2000 decreases the frequency of alcohol consumption.Hypothesis 5.3: The prevention program Klasse2000 decreases the probability of smoking cigarettes.Hypothesis 5.4: The prevention program Klasse2000 decreases the smoking frequency.

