Intervention effects in the following domains are assessed: well-being, health-related behavior, classroom atmosphere, school violence, alcohol and tobacco consumption, and media use. These domains are investigated from the perspective of the students and their parents. Klasse2000 is a large universal prevention program. It is financially supported with donations from well-known institutions such as health care providers and banks and endorsed by experts of national recognition [21]. The program has received the highest possible rating category from the green list prevention provided by the Crime Prevention Council of Lower Saxony. Furthermore, it has received several awards [21]. Given this high status, the results of this study potentially have far-reaching consequences not only for the program at hand but, depending on the nature of results, on other preventions with similar target areas. It is likely that this evaluation will not confirm all hypotheses stated in this protocol. The failure to find and intended intervention effect might be due to a lack of effect or the presence of a meaningful but undetectable effect. Should the intervention fail to produce some of the desired effects, it might warrant improvement. The materials of the Klasse2000 intervention are regularly updated. These updates attempt to improve support for teachers in the implementation, communication with parents, and communication of teaching content to the students. Recent updates include, for example, content for DigiBoards (Digi International) and an interactive website for the students; further digitalization and extension of online health-related content is planned [21]. Depending on the areas that might warrant improvement, successful concepts from eHealth interventions might provide fruitful starting points. Through the wide implementation of the Klasse2000 program, even small effects might be of value from a public health perspective. Future evaluation studies might want to address this issue using assessment tools that assess the targeted health-related behaviors more reliably. Expertise with mobile assessment from the eHealth domain could help future evaluations to quantify small effects.

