### Limitations

The main limitation of the study is the missing randomization. The main problems of missing randomization are potential selection effects at the school level. Schools that are problem-prone might be more likely to participate in the Klasse2000 program, hoping that participation might reduce prevailing problems. On the other hand, the exact opposite might also be the case. Schools that can be characterized as especially committed and dedicated might decide to participate in the Klasse2000 program. Such selection effects might be counterbalanced with the propensity score-matching approach. It should also be noted that the study design does not include any measurement prior to the intervention. This is a cross-sectional survey that can identify correlations but cannot map causal relationships. The results should be checked within the framework of a longitudinal study design and a preliminary survey and offer necessary space for future research projects.

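### Eleven hypotheses are primary with no hierarchy or joint success rule, while the only error rate and sidedness given are those of a single unadjusted one-tailed test

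*Protocol article*

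**What the plan says.** Under Evaluation of Effectiveness, research questions 1 (well-being) and 2 (health-related behavior) are each called a primary outcome domain. The third is primary as well: "Research question 3 (school and classroom atmosphere, school-based conflicts, and violence; primary outcome". They contain hypotheses 1.1 to 1.4, 2.1 to 2.4 and 3.1 to 3.3, all worded as an improvement due to the program. Research questions 4 and 5 are secondary and add nine hypotheses. The same section separates primary from secondary by how probable an effect is thought to be, not by how error is to be controlled.

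Under Data Analysis, the power calculation is "based on a type I error rate (false positive) of α=.05", "statistical power of 1−β=.80" and "a minimum detectable effect size of ES=0.2", leading to "n=310 (1-tailed) students in each group". No other alpha or sidedness appears. The outcome analyses are described only as regression-based and using the matching weights. Subgroup analyses of the same hypotheses are announced.

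The Discussion (Summary) speaks of hypotheses being confirmed or not, one by one, and adds: "These domains are investigated from the perspective of the students and their parents".

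**The concern.** A study with 11 primary hypotheses that may each be confirmed separately needs either a ranking or a rule that controls error across them. The document fixes the number of primary hypotheses and, separately, an error rate that fits only one of them. Data Analysis itself cites the large number of outcomes as a reason why randomization was infeasible, yet its error rate takes no account of that number.

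Sidedness matters too. If the analyses are one-tailed for benefit, like the sample size, a difference against the program has no route to being called significant, however large. The Summary expects potentially far-reaching consequences from the results, and the program has reached more than 1.4 million children. Both a chance confirmation and an unreported adverse difference would therefore matter.

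**Working it through.** **Inputs from the article.** Alpha .05, one-tailed, power .80, ES 0.2, 310 per group (Data Analysis). 11 primary and 9 secondary hypotheses (Evaluation of Effectiveness). Students: 2371 Klasse2000, 4005 control (Abstract, Results). Parents: 1205 and 2119 (Trial Status Upon Submission of Protocol Revision).

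**Assumptions.** ES is a standardized mean difference with SD 1. The design effect for clustering is 1.8 to 2.6; the article gives none. No further loss from propensity weighting is included.

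**1. The plan's own figure.** n per group = 2(z₀.₉₅ + z₀.₈₀)² / 0.2² = 2(1.645 + 0.842)² / 0.04, which rounds up to 310. A noncentral t check gives power 0.800 at 310. The two-sided version, 2(1.960 + 0.842)² / 0.04, gives 393. The stated 310 is therefore the size for one one-tailed test at an unadjusted .05.

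**2. Chance of at least one false primary confirmation, all nulls true, 11 one-tailed tests at .05.** Under independence this is 1 − 0.95¹¹ = 0.431. With equally correlated normal test statistics:

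| Common correlation | Chance |
|---|---|
| 0 | 43.1% |
| 0.1 | 39.5% |
| 0.3 | 32.5% |
| 0.5 | 25.9% |
| 0.7 | 19.3% |

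The Bonferroni upper bound is 11 × .05 = 55%.

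**3. Two-sided testing alone.** With two-sided .05 tests, a false confirmation of benefit has probability .025 per test, so under independence 1 − 0.975¹¹ = 24.3%. Changing sidedness does not replace joint control.

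**4. Direction.** With a true effect of −0.2 and 310 per group, a one-tailed test for benefit rejects with probability about 0.00002, and any such rejection would be in the wrong direction.

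**5. Cost of control at the strictest Holm step.** Two-sided .05/11 = .00455, z = 2.84. At ES 0.2 and power .80 this needs 677 per group before clustering; at 310 per group power would be 0.36. For the achieved samples, detectable difference = (2.84 + 0.84) × √(1/n₁ + 1/n₂) × √(design effect):

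- Students: √(1/2371 + 1/4005) = 0.0259. 3.68 × 0.0259 × √1.8 = 0.128, and with √2.6 it is 0.154.
- Students, if matching were 1:1 (2371 and 2371): √(2/2371) = 0.0290, giving about 0.14 to 0.17.
- Parents: √(1/1205 + 1/2119) = 0.0361. 3.68 × 0.0361 × √1.8 = 0.178, and with √2.6 it is 0.214.

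**The case against.** The strongest reply is that alpha and the one-tailed label stand only in the sample-size sentence. The analysis text gives no alpha, sidedness or decision rule, and a multiplicity procedure may sit in an analysis plan that is not shown. This stands in part. The article does not say that each hypothesis will be tested one-tailed at .05, and the absence of a named procedure is not itself the point. What remains is stated in the article: 11 hypotheses made primary without ranking, beside an error rate and sample size built for one one-tailed test.

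Several stronger readings are tempting but not supported:

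- A reader might infer that a false confirmation is more likely than not. For the 11 primary hypotheses the chance is below one half even under independence. It passes one half only with more tests, for example all 20 hypotheses under independence (1 − 0.95²⁰ = 64%).
- A reader might count 22 tests because there are two informants. The Summary says the domains are viewed from both perspectives, not that each hypothesis is tested twice.
- A reader might infer that harm cannot be detected. Weighted regression gives signed estimates, and nothing rules out two-sided intervals. The restriction applies only if the tests are one-tailed.
- A reader might cite the Limitations, "On the other hand, the exact opposite might also be the case", as evidence that the program could do harm. That sentence concerns which schools choose the program, so it is about confounding. A two-sided test would not separate the two.

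It is also fair that the article sets no rule declaring the program effective on any single success, and that the Limitations disclaim causal conclusions. This softens the consequence but does not supply the missing rule.

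**Conclusion.** The point holds in a conditional form and should be addressed. As written, the document pairs 11 unranked primary hypotheses with the error rate of one one-tailed test. If the primary analyses follow that basis, the chance of at least one false primary confirmation is about 26% to 43% for common correlations from 0.5 down to zero, and 19% even at 0.7, against a nominal 5%. An adverse difference could not be declared significant. These figures assume that all 11 nulls are true and that there is one test per hypothesis. Hypotheses that bundle several outcomes, such as 2.3, would raise them if split.

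**What to change.** State in the analysis plan, before hypothesis tests are run:

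- Primary analyses use two-sided tests with 95% confidence intervals.
- Holm is applied across the 11 primary hypotheses, or alpha/3 (.0167) per domain with Holm inside each domain.
- The confirmatory test uses the student report where it exists, with the parent report as supportive.
- Research questions 4 and 5 and the subgroup analyses are not confirmatory.

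The article says that no hypothesis-related results had been obtained at resubmission. It also expected results in mid-2020, so any test run before the change should be reported as such.

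The cost is some power per test. In the student data the detectable difference at the strictest step is about 0.13 to 0.15 SD, below the planned 0.2, under the assumed design effect and before any loss from weighting. In the parent data it is about 0.18 to 0.21 SD, so the margin is not assured; this is a further reason to lead with the student report. The SD scale does not carry over directly to the bullying hypotheses (3.2 and 3.3), which concern probabilities and need their own calculation.

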### Evaluation of Effectiveness

It is of special interest whether the underlying constructs are based on the direct efficiency hypothesis of the Klasse2000 program (primary outcome) or based on an efficiency hypothesis but one that must be regarded as less probable than the primary outcome (ie, secondary outcome). For some outcomes (such as alcohol and tobacco consumption), the expected prevalence is generally low.

The evaluation focuses on the following research questions:

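### The stated requirement of 310 students per group assumes independent students and omits the clustering by class and school, so it is too low as a requirement, although the sample obtained is large enough for ES=0.2

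*Protocol article*

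**What the plan says.** The power statement in Data Analysis has four inputs: a "type I error rate (false positive) of α=.05", a "statistical power of 1−β=.80", a "minimum detectable effect size of ES=0.2" and a one-tailed test. From these, the article reports that they "resulted in a required sample size of n=310 (1-tailed) students in each group (intervention and control". It does not name the metric of the effect size, and it gives no ICC, cluster size or design effect.

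Elsewhere the article describes a clustered design. Sample and Sampling says that 600 classes were drawn at random, that 140 further program classes were added, and that assessment was by classroom. Data Analysis says that schools choose whether to adopt the program, so exposure does not vary within a school. The same section plans regression with weights on the control students. The target was 8000 students. The abstract reports 6376 obtained, 2371 in Klasse2000 and 4005 controls.

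**The concern.** Students in one class share a teacher, a peer group and, for several hypotheses, the very thing being measured (classroom atmosphere, bullying). Their answers are likely to be correlated, and all students in a school have the same exposure. A sample-size figure counted in students and computed as if they were independent then promises more precision than the design delivers.

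What is at stake is interpretation. The 310 is the only figure in the article for what the study can detect. A reader who sets 2371 and 4005 against it would credit the study with more sensitivity than it has. The Summary in the Discussion says that a failure to find an effect might mean no effect or "the presence of a meaningful but undetectable effect". To tell these apart, one needs a detectable effect that fits the design.

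**Working it through.** **Inputs from the article.** One-sided α = 0.05 (z = 1.645), power 0.80 (z = 0.842), effect 0.2, equal groups, stated n = 310 (Data Analysis). Sample obtained: 2371 and 4005 students (Abstract), 1205 and 2119 parents (Results). The article allows two estimates of students per class, m:
- 8000 / (600 + 140) = 10.8, from Sample and Sampling;
- 60,000 / 2800 = 21.4, from the Klasse2000 Program section.

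**Assumption.** The documents give no ICC. The range 0.01 to 0.20 is assumed here.

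**Step 1: reproduce 310.** n = 2 × ((1.645 + 0.842) / 0.2)² = 309.13, rounded up to 310. With the noncentral t distribution, power is 0.7991 at 309 and 0.8002 at 310 per group. The two-sided version gives 393 and does not match. The figure is therefore the unclustered one-sided result, with nothing added.

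**Step 2: add the clustering.** Formulas:
- design effect DE = 1 + (m − 1) × ICC;
- required n = 309.13 × DE;
- power with 310 per group = Φ(0.2 / √(2 × DE / 310) − 1.645);
- power with the sample obtained = Φ(0.2 / √(DE × (1/2371 + 1/4005)) − 1.645);
- power with a 1:1 match = Φ(0.2 / √(2 × DE / 2371) − 1.645);
- one-sided minimum detectable effect (MDE) of the sample obtained = 2.4865 × √(DE × (1/2371 + 1/4005)).

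| m | ICC | DE | n per group needed | Power with 310 | Power, 2371 vs 4005 | Power, 2371 vs 2371 | MDE (SD) |
|---|---|---|---|---|---|---|---|
| 10.8 | 0.01 | 1.10 | 340 | 77% | >99.9% | >99.9% | 0.068 |
| 10.8 | 0.05 | 1.49 | 461 | 65% | >99.9% | >99.9% | 0.079 |
| 10.8 | 0.10 | 1.98 | 613 | 55% | >99.9% | 99.9% | 0.091 |
| 10.8 | 0.20 | 2.96 | 916 | 42% | 99.8% | 99.1% | 0.111 |
| 21.4 | 0.01 | 1.20 | 373 | 73% | >99.9% | >99.9% | 0.071 |
| 21.4 | 0.05 | 2.02 | 625 | 54% | >99.9% | 99.9% | 0.092 |
| 21.4 | 0.10 | 3.04 | 941 | 41% | 99.7% | 98.9% | 0.112 |
| 21.4 | 0.20 | 5.09 | 1573 | 29% | 96.2% | 92.1% | 0.145 |

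**Step 3: break-even.** The 1:1 matched sample falls below 80% power at 0.2 only when DE exceeds 2371 / 309.13 = 7.67. At m = 21.4 that means an ICC above (7.67 − 1) / 20.4, about 0.33.

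**Step 4: parent reports.** √(1/1205 + 1/2119) = 0.0361, against √(1/2371 + 1/4005) = 0.0259 for students. At the same DE the MDE is thus 1.39 times larger, about 0.09 to 0.20 SD. The upper end is cautious, because only 52.13% of parents replied. With 21.4 × 0.5213 = 11.2 parents per class and ICC 0.20, DE is 3.03 and the MDE is 2.4865 × 0.0361 × √3.03, about 0.16 SD.

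No line above includes a loss from weighting, which the article does not quantify.

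**The case against.** The strongest reply is that 310 is correct for its stated inputs and did no harm. The arithmetic reproduces exactly, the article never says that 310 set the target, and the survey obtained many times that number. All of this stands. The defect is an unstated independence assumption, not a slip in calculation, and it costs the study no students.

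Several stronger readings are tempting, and the documents do not support them.

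- *The study is underpowered at 0.2.* The 77% to 29% describes a study of 310 per group that was neither planned nor run. The sample obtained keeps 96% or more over the assumed range.
- *310 cannot apply to binary outcomes.* Read as Cohen's h, an effect of 0.2 gives the same 309.13 by the arcsine formula. The fair point is that the metric is not named. This matters most for outcomes of which the article says "For some outcomes (such as alcohol and tobacco consumption), the expected prevalence is generally low".
- *The article contradicts itself because "effect sizes in universal prevention programs can be expected to be rather small".* That remark explains why randomization was infeasible and gives no number. An effect of 0.2 is conventionally called small.
- *310 conflicts with the target, "Overall, we aimed for the total sample to consist of 8000 students and their parents".* Planning to exceed a minimum is no inconsistency.
- *The remark on undetectable effects relies on 310.* It cites neither 310 nor 0.2 and would be true of any finite sample. It shows only where a correct figure would be useful.

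Nor can a fuller document rescue the number. The article states the inputs, the result and the unit, and the result equals the unclustered one, so no design effect can be hidden in it.

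**Conclusion.** The stated requirement is wrong for this design. It is certain that 310 students per group give less than 80% power at 0.2 for any ICC above zero. The size of the shortfall rests on an assumed ICC and on class sizes inferred from the article's totals: a requirement of about 340 to 1,570 per group instead of 310.

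The conclusion that the study itself is adequate at 0.2 also has limits. It ignores weighting loss and treats the class as the cluster. The article does not say how many classes came from one school, and school-level clusters would raise the design effect. As an illustration, with an assumed 40 students per school, the 1:1 match keeps 84% power at ICC 0.15 and falls to 75% at ICC 0.20, while the full 2371 versus 4005 keeps 83% at ICC 0.20.

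This is a minor to moderate point about a stated figure and how results will be read against it. It changes no sample, estimator or test.

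**What to change.** 1. Replace 310 with a requirement that includes a design effect, and label the ICC and cluster size as assumptions with a range.
2. Name the effect-size metric (standardized mean difference, Cohen's h or other).
3. State the minimum detectable effect of the clustered sample obtained: about 0.07 to 0.15 SD, one-sided, over the range used here and before weighting loss. Say that it is larger for parent reports. The actual numbers of classes and schools should replace the inferred cluster sizes.
4. Use that detectable effect, not 310, when interpreting non-significant results.

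The cost is recalculation and a few sentences, with no further data collection. The stated requirement becomes less favourable than 310, but the sample obtained still exceeds it over the range in the table. The Results section says that no hypothesis-related results had been obtained at resubmission, so as of this document the correction can precede them.
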